## Aims

The aim of this study is to use two-sample Mendelian randomization to estimate the effect of various previously reported preventive therapies on CRC risk.

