For those molecular traits that will be taken forward for further analyses, genetic instruments will be constructed by identifying GWASs that have reported genetic associations with direct measures of molecular traits of interest in populations of European ancestry. These studies, and available instruments, will be searched for using several databases. Firstly, the GWAS catalogue
^
27
^ and the IEU Open GWAS
^
28
^ will be searched, followed by PubMed and medRxiv/bioRxiv for any pre-prints. We will also consult in-house summary genetic association statistics, if necessary, to access restricted and unpublished datasets. Genetic instruments will be constructed by selecting SNPs strongly associated with each trait of interest (p<5°10
^-8^) using summary genetic association data from these studies. For those molecular traits that are protein drug targets or biomarkers, SNPs will be selected that are located in or within proximity to genes that code for that protein (termed
*cis*-variants).
*Cis*-variants are expected to be specific to the target being instrumented which should minimise the likelihood of bias from horizontal pleiotropy. In addition, the use of
*cis*-acting variants that influence protein targets of drugs examined would be expected to enhance instrument strength because protein expression is relatively proximal to germline genetic variants. In the absence of SNPs associated with direct measures of protein targets, we will explore constructing instruments from SNPs associated with downstream biomarker perturbations of drug targets. For those molecular traits that correspond to dietary agents or endogenous hormones, genome-wide significant variants will be selected independent of their genomic position. Of these variants, only those that are independent (r
^2^<0.001) will be included as instrumental variables in the primary analyses. For protein drug targets and biomarkers, we will increase the number of SNPs in our genetic instrument by permitting SNPs to be in weak linkage disequilibrium (e.g. r
^2^<0.10). We will account for this by generating a correlation matrix using a random subset of 10,000 individuals of white British ancestry in the UK Biobank as reference panel and using a generalised IVW method that can account for correlated instruments
^
29
^.

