## Study status

At the time of submission of this protocol for publication, preventive agents have been identified from the literature and we have identified the corresponding molecular trait for each agent. We have determined which molecular traits are instrumentable and, for those that are (
Table 2), we have begun to identify genetic instruments.

**Table 2. T2:** Preventive agents identified in the literature to be associated with CRC risk reduction.

Preventive agent	Molecular trait
Dietary long-chain omega-3 polyunsaturated fatty acids	Circulating long-chain omega-3 polyunsaturated fatty acids
Dietary long-chain omega-6 polyunsaturated fatty acids	Circulating long-chain omega-6 polyunsaturated fatty acids
Dietary salicylic acid	Plasma salicylic acid levels
Dietary calcium	Serum calcium levels
Dietary vitamin D	Serum 25 hydroxyvitamin D
Dietary folate levels	Serum folate levels
Dietary selenium	Circulating selenium levels
Dietary vitamin A	Serum retinol levels
Dietary vitamin C	Plasma vitamin C levels
Dietary vitamin E	Circulating alpha-tocopherol levels
Dietary β carotene	Circulating β carotene levels
Dietary magnesium	Serum magnesium levels
Statins	Circulating LDL cholesterol levels (due to HMG-CoA reductase inhibition)
Guselkumab	Plasma IL23 protein levels
Antihypertensives	Serum ACE levels
	SBP (due to NCC inhibition)
	SBP (due to ADRB1 inhibition)
Testosterone	Circulating testosterone levels
Estradiol	Serum estradiol levels
Sex hormone binding globulin	Serum SHBG levels
Progesterone/17- hydroxyprogesterone	Circulating progesterone/17- hydroxyprogesterone levels

Abbreviations: CRC = colorectal cancer; LDL = low-density lipoprotein; HMG-CoA = 3-hydroxy-3-methylglutaryl coenzyme A; IL23 = interleukin 23; ACE = angiotensin-converting enzyme; SBP = systolic blood pressure; NCC = sodium chloride cotransporter; ADRB1 = β1 adrenoceptor; SHBG = sex hormone binding globulin. Preventive agents identified in the literature that had a corresponding molecular trait that was deemed instrumentable. These agents included dietary micronutrients, drugs and endogenous hormones. For each drug, the biological target of the drug was identified as it’s molecular trait, (e.g. the levels of the protein that the drug targets). For dietary micronutrients and endogenous hormones, molecular traits were identified that correspond to the agent (e.g. blood-based biomarkers for vitamin levels).

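### The serum ACE and plasma IL23 instruments are not tested against an established effect of the drugs they stand for, so the plan cannot tell whether their CRC estimates speak to the drug

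*Protocol article*

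**What the plan says.** The Aims section sets out to "estimate the effect of various previously reported preventive therapies on CRC risk". Under Exposure data and instrument selection, the exposure for a drug is its biological target, instrumented by genome-wide significant cis-SNPs. Two reasons are given for relying on them. The first is that cis-"variants are expected to be specific to the target being instrumented which should minimise the likelihood of bias from horizontal pleiotropy". The second is that they should be strong, because protein expression lies close to the germline variant.

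A downstream marker of drug action is used only as a fallback: "In the absence of SNPs associated with direct measures of protein targets, we will explore constructing instruments from SNPs associated with downstream biomarker perturbations".

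Table 2 (Study status) has five drug rows:
- Statins: LDL cholesterol, through HMG-CoA reductase inhibition.
- Antihypertensives: SBP through NCC inhibition, and SBP through ADRB1 inhibition.
- Antihypertensives: "Serum ACE levels".
- Guselkumab: "Plasma IL23 protein levels".

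The first three rows are scaled by something the drug is meant to change. The last two are scaled by how much of the target protein is measured in blood.

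**The concern.** The plan describes drug action as inhibition of a target. Using the circulating level of that target as the exposure assumes that a genetically lower level does what inhibition does. Specificity for the gene limits pleiotropy through other pathways, and strength limits weak-instrument bias. Both can hold in full while the measured level tracks target activity poorly, not at all, or in the opposite direction.

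The fallback rule has a side effect. Once a protein-level SNP exists, the downstream marker is not called on, so the link to drug action that the other three rows carry is lost for ACE and IL23.

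What is at stake is the meaning of two results. If the instrument does not mimic the drug, a null says little about the drug and a signal could carry the wrong sign. The article applies the same principle elsewhere: it excludes drugs such as metformin whose mechanism is not well enough understood to instrument.

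**Working it through.** **1. Does any listed check test mimicry of the drug?**

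| Check (section) | What it addresses |
|---|---|
| R² and F > 10 (Main analyses) | Strength against the measured level |
| Multivariable MR (Main analyses) | Genetic overlap between instruments, for FDR-significant findings |
| Sample-overlap analyses (Outcome data) | Weak-instrument bias from shared participants |
| Leave-one-out (Sensitivity analyses) | Influence of single SNPs |
| Weighted median, weighted mode, MR-Egger, supported by MR-PRESSO (Sensitivity analyses) | Horizontal pleiotropy; the first three need about 10 or more independent SNPs |
| Steiger filtering (Sensitivity analyses) | Reverse causation; run only after an FDR-significant result, so a null never triggers it |
| Coloc and SuSiE (Colocalisation) | Shared causal variant between the trait and CRC |

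None compares the ACE or IL23 instrument with an effect the drug is known to have.

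**2. How precise could an uninformative null look?**

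Inputs from the Power section: 78,473 cases, 107,143 controls, 5% significance level, R² of 0.001, 0.005, 0.01 and 0.05, and an OR of 0.8 as the middle of its three effect sizes. A two-sided test is assumed, since the article does not say.

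The plan's own total reproduces: 78,473 + 107,143 = 185,616. The power values are in a figure that is not shown, so they cannot be compared.

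Using the usual approximation for a binary outcome, with p = 78,473/185,616 = 0.4228:

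- N·p·(1−p) = 78,473 × 107,143 / 185,616 ≈ 45,297
- SE(log OR) = 1/√(45,297 × R²)
- CI centred on OR 1 = exp(±1.96 × SE)
- Power at OR 0.8 = Φ(0.2231/SE − 1.96), where 0.2231 = |ln 0.8|

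| R² | SE | Null-centred 95% CI | Power at OR 0.8 |
|---|---|---|---|
| 0.001 | 0.149 | 0.75–1.34 | 32% |
| 0.005 | 0.066 | 0.88–1.14 | 92% |
| 0.01 | 0.047 | 0.91–1.10 | 99.7% |
| 0.05 | 0.021 | 0.96–1.04 | about 100% |

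An OR of 0.8 lies inside the interval at R² = 0.001 and outside it at the other three values.

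**3. Illustration of imperfect mimicry (assumed values).**

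Assume a true OR of 0.8 per SD of target activity in the drug's direction, and let ρ be the SD change in activity per SD of the instrumented level. The expected log OR is then ρ × ln 0.8. At R² = 0.01:

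| ρ | Expected OR | 95% CI | Chance of a significant result |
|---|---|---|---|
| 1 | 0.80 | 0.73–0.88 | 99.7%, correct direction |
| 0.2 | 0.96 | 0.87–1.05 | 16%, correct direction |
| 0 | 1.00 | 0.91–1.10 | 5%, either direction |
| −0.5 | 1.12 | 1.02–1.23 | 66%, wrong direction |

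The checks in step 1 do not estimate ρ. A positive control would not measure it exactly, but it would test whether the relation to drug action is present and in which direction.

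**The case against.** The quoted sentence claims only specificity and less pleiotropy, and that is not in dispute. The article is condensed, instruments were still being identified when it was submitted, and a fuller plan might contain a positive control. The methods also describe the estimate as the effect of the molecular exposure, and Table 2 has a separate column naming the trait. On that reading nothing is misstated.

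Part of this stands. A reader might infer that a null on ACE or IL23 will be taken as a verdict against the drug. The article does not say so; the step follows only from the therapy-level aim together with Table 2. A reader might also infer that such a null will be precise. That depends on R², which is not given for either row, and at 0.001 it would not be. Nor do the documents show that either instrument misrepresents its drug.

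It is also tempting to object that the three antihypertensive rows are on different scales. No comparison or pooling of those rows is planned, and rescaling ACE to SBP would cut across the rule that keeps downstream markers for targets without protein-level SNPs. That objection is not made here.

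The appeal to condensation does not dispose of the point. The article sets out its selection rules, sensitivity analyses and even its colocalisation priors, and it states why cis-instruments are to be trusted. That reason leaves drug mimicry uncovered, and the listed checks, followed exactly, could still lead to a drug-level conclusion.

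**Conclusion.** The point holds as a gap in the design for two of the five drug rows. Serum ACE and plasma IL23 stand in for drugs on grounds of specificity and strength alone, and nothing planned tests whether their instruments reproduce an established drug effect. It is a gap in what can be concluded, not a demonstrated error in either instrument.

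Its size depends on R². If R² is 0.005 or more and the instrument does not mimic the drug, a null-centred interval would appear to rule out an OR of 0.8. At R² = 0.001 it would not. These figures rest on the standard variance approximation and a two-sided 5% level. The ρ values are illustrative and come from no document.

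**What to change.** Before examining the CRC estimates for these two rows, write down a positive-control MR for each protein-level instrument. The CRC statistics are public, so this is a matter of fixing the order and the rule in advance, not of blinding.

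- **Serum ACE:** use SBP as the control outcome. It is already the scale of the NCC and ADRB1 rows, and ACE is listed as an antihypertensive target, so the expected direction is clear.
- **Plasma IL23:** name an outcome on which the drug has an established effect and for which summary data are available. The article gives none, so the authors must choose and justify it.
- **Reporting:** give the control's estimate, 95% CI and power, because a control can also fail through imprecision.
- **Rule:** draw a conclusion about the drug, null or positive, only if the control is in the expected direction. If it is absent, reversed or too imprecise, report the CRC result as evidence on the circulating protein only.

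The cost is two extra analyses on summary data, and possibly a row that supports no conclusion about its drug. Instrument identification had only begun at submission, and the Dissemination section already provides for reporting changes in methodology.

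### For the statin, NCC and ADRB1 rows, map position is the SNPs' only tie to the drug target's gene, and no planned check would show that a single-signal instrument acts through a neighbouring gene

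*Protocol article*

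**What the plan says.** All of this is in the protocol article.

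- **Selection (Exposure data and instrument selection).** "Genetic instruments will be constructed by selecting SNPs strongly associated with each trait of interest", at p<5×10^-8. For protein drug targets and biomarkers, "SNPs will be selected that are located in or within proximity to genes that code for that protein (termed" cis-variants). No distance is given.
- **Reason for trusting them (same section).** Cis-"variants are expected to be specific to the target being instrumented which should minimise the likelihood of bias from horizontal pleiotropy". They are also expected to be strong instruments "because protein expression is relatively proximal to germline genetic variants".
- **Fallback (same section).** Without SNPs for the protein itself, "we will explore constructing instruments from SNPs associated with downstream biomarker perturbations of drug targets".
- **Where the fallback applies (Study status, Table 2).** Three rows already listed as instrumentable: "Circulating LDL cholesterol levels (due to HMG-CoA reductase inhibition") for statins, and "SBP (due to NCC inhibition") and "SBP (due to ADRB1 inhibition") for antihypertensives. The other two drug rows, IL23 and ACE, use levels of a protein.
- **Checks planned (Main analyses, Sensitivity analyses, Colocalisation).** Leave-one-out for multi-SNP instruments; weighted median, weighted mode and MR-Egger when there are about 10 or more independent SNPs; MR-PRESSO; Steiger filtering and multivariable MR for FDR-significant findings; coloc of the molecular trait with colorectal cancer (CRC), a multiple-causal-variant method such as SuSiE, and regional plots.

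**The concern.** When the measured exposure is the gene's own protein, a nearby SNP that changes the protein level is tied to that gene by the exposure association itself. When the exposure is LDL or SBP, the association shows only that the SNP moves a trait influenced by many genes. Which gene it acts through is then inferred from position alone. The justification given in the protocol is the protein one, and it is carried over to rows where no protein is measured.

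At stake is what these rows can conclude. Table 2 labels the exposure as due to inhibition of a named target, and the aim is to estimate effects of preventive therapies. A positive or null result would be read as evidence about statins, NCC inhibitors or ADRB1 blockers. If the instrument acts through a neighbouring gene, the result says nothing about the drug.

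**Working it through.** **1. Count the rows.** Table 2 has 12 dietary rows, 5 drug rows and 4 hormone rows: 12 + 5 + 4 = 21. The fallback covers 3 of the 5 drug rows, so 3 of 21.

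**2. Set each planned check against the question of which gene the SNP acts through.**

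| Check | What it compares | Can it show the wrong gene? |
|---|---|---|
| Genome-wide threshold | SNP with LDL or SBP | No |
| Leave-one-out | One SNP against the rest | Can flag one discordant SNP among several; not with one SNP, nor reliably where several SNPs tag one signal |
| Weighted median, mode, Egger, MR-PRESSO | SNPs against each other | Same limit |
| Steiger | Trait with CRC | No, direction only |
| Multivariable MR | Overlap between instruments under study | No, neighbouring genes are not under study |
| coloc | Trait with CRC | No, if one variant drives both |
| SuSiE, regional plots | Trait with CRC, several signals | Can show that only one of several signals is shared; not with one signal |

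**3. Does coloc pass a wrong-gene variant when there is one signal?** The outcome sample reproduces the protocol's total: 78,473 + 107,143 = 185,616, with case fraction k = 0.4228. The following are assumptions, not from the documents: biomarker GWAS of 400,000; MAF 0.3; biomarker effect 0.06 SD per allele; a 500-SNP region; CRC log-OR of 0.03, 0.05 or 0.07 per allele through a neighbouring gene; 300 runs per setting.

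- Biomarker SE = 1/√(2 × 0.3 × 0.7 × 400,000) = 0.00244, so expected z = 0.06/0.00244 = 24.6.
- CRC SE = 1/√(2 × 0.3 × 0.7 × 185,616 × 0.4228 × 0.5772) = 0.00725, so expected z = 4.1, 6.9 and 9.7.

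| CRC log-OR | 0.03 | 0.05 | 0.07 |
|---|---|---|---|
| Wald ratio nominally significant | 97% | 100% | 100% |
| PPH4 >0.50, default priors | 79% | 100% | 100% |
| PPH4 >0.80, default priors | 62% | 99.7% | 100% |
| PPH4 >0.80, p12 = 1×10^-6 | 35% | 92% | 98% |
| Contrast: distinct variants, LD r² 0.40, PPH4 >0.50 | 8% | 3% | 0% |

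Colocalisation therefore does its own job of rejecting distinct variants in LD. It mostly passes a shared variant whatever gene that variant acts through, because H4 is then true.

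**4. What if there are several signals?** Take three equally weighted SNPs, one contaminated with CRC z = 5.5 and the others at zero. The protocol prescribes fixed-effects IVW for about three SNPs or fewer, so z = 5.5/√3 = 3.18, p ≈ 0.0015. This is below the first-rank FDR cut of 0.05/21 = 0.0024. Dropping the contaminated SNP gives an expected z of 0/√2 = 0, so leave-one-out flags it. In simulations of three nearly independent biomarker signals of equal strength, PPH4 exceeded 0.50 in 37% and 46% of runs in two sets. It did so in 0% when the contaminated signal was the weaker one and in 97–98% when it was dominant.

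**5. How likely is it?** With L significant biomarker loci spread evenly over an assumed 2,875 Mb, the chance that a window of W Mb holds an unrelated one is 1 − exp(−L × W/2,875). For L = 100, W = 0.2 this is 0.7%; for L = 1,000, W = 2 it is 50%. The documents give neither L nor W. The formula also leaves out the further condition that the locus affects CRC.

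**The case against.** The strongest reply is that the planned checks are better than they first appear. Leave-one-out is aimed at a SNP that drives the result, and step 4 shows that it catches one bad SNP in three. SuSiE and regional plots can show that only one of several signals is shared with CRC. Colocalisation does not automatically return H4. All of that stands and confines the point to instruments with one SNP or one signal.

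Several stronger readings are tempting but unsupported:

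- **That SNPs are chosen only for position.** They must also reach p<5×10^-8 with LDL or SBP. Position is the only link to the gene, not the only criterion.
- **That every planned check would be passed.** Not where several distinct signals are available.
- **That the pleiotropy-robust models will not be run for these rows.** No SNP counts are given, the cut-off of 10 is only an example, and relaxing r² to 0.10 is meant to add SNPs.
- **That 0.7% to 50% is the chance of a wrong answer.** It is the assumed chance of an unrelated biomarker locus in a window, not of one that also affects CRC. The joint chance must be lower.
- **That these rows are biased.** Nothing in the documents shows a neighbouring gene at work at any of the three loci.

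It can also be said that this is a condensed article, that the authors only propose to explore such instruments, and that per-locus validation belongs in a fuller plan. This stands only in part. The article itself states both the selection rule and its justification, and Table 2 already lists the three rows as instrumentable. The point is that the stated justification does not fit them, not that detail is missing.

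**Conclusion.** The point holds in limited form. For the statin, NCC and ADRB1 rows, the protocol's reason for regarding cis-SNPs as target-specific does not apply, because the exposure is a downstream trait and position is the only tie to the gene. If such an instrument rests on one SNP or one signal, no planned step would show that it acts through a neighbouring gene.

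The size is possible misattribution in up to three of 21 rows. Its probability cannot be derived from the documents, and the simulated pass rates hold only under the effect sizes and sample size assumed above. The other 18 rows are not affected by this point. It is worth acting on because the remedy is cheap, can still be pre-specified (Study status says instrument identification has only begun), and changes what these rows may be said to show.

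**What to change.** Keep the primary instruments. Under Exposure data and instrument selection and Sensitivity analyses, add for the three downstream-biomarker rows a pre-specified sensitivity analysis:

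1. Colocalise the LDL or SBP signal with expression of the target gene and of neighbouring genes in public eQTL data, naming the tissues beforehand, or note a protein-altering variant in the target gene. The protocol's own PPH4 bands can be used.
2. Repeat the MR with SNPs inside the target gene only.
3. Where the tie to the target gene is unsupported or cannot be tested, report the row as locus-level evidence and not as an effect of the drug.

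This should not become a rule for dropping SNPs. Relevant tissue data may be missing, power may be low, and a variant may regulate several genes at once, which is why neighbouring genes belong in step 1. Step 2 is still positional, so it supports but does not settle the matter.

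The cost is a few extra coloc runs at three loci with software already planned. The downside is that some rows may carry a weaker label where tissue data are lacking.

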### Main analyses

The proportion of variance in the molecular traits explained by the SNPs used as instrumental variables (r
^2^) and the strength of the instrument (F-statistic) will be calculated. The F-statistic can be used to test the “relevance” assumption and a threshold of >10 indicates that weak instrument bias is unlikely
^
35
^.

The proportion of variance explained in the instruments (R2) will be calculated using the following formula: 

$$R^{2}=\frac{2\beta^{2}MAF(1-MAF)}{2\beta^{2}MAF(1-MAF)+{\left(se(\beta )\right)}^{2}(2N)MAF(1-MAF)}$$

Where β is the effect size (beta coefficient) for a given SNP, MAF is the minor allele frequency, se(β) is the standard error of the effect size, and N is the sample size. 

F-statistics will be calculated using the following formula:

$$F=R^{2}(N-2)/(1-R^{2})$$

Where R2 is the proportion of variance explained in the instrument, N is the sample size

For molecular traits instrumented by a single SNP, the Wald ratio will be used to calculate the effect of the molecular exposure on CRC risk
^
23
^. For those traits that are instrumented by more than one SNP, the inverse-variance weighted (IVW) method will be used
^
23
^. The multiplicative random effects IVW will be prioritised, except where the number of SNPs is limited (e.g. ≤3) in which case the fixed effects IVW will be used.

To account for multiple testing, we will use a false discovery rate (FDR) correction of <5% to define strong evidence.

We will attempt to explore analyses stratifying by cancer subsite (e.g. distal, proximal, colon, and rectal). This will require requesting access for restricted GWAS data
^
36
^.

We will explore conducting multi-variable MR (MVMR)
^
37
^ for significant findings (reaching an FDR corrected threshold of <5%) for which there is genetic overlap between instruments. We will use MVMR when we suspect this genetic overlap is more likely to reflect horizontal, as opposed to vertical, pleiotropy.

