### Sensitivity analyses

For instrumental variable sets that use more than one genetic instrument, the analyses will be iteratively repeated, each time leaving out one SNP to test if there is a particular SNP that is driving results, which could be due to the outlying SNP being the only valid instrument or due to this SNP being horizontally pleiotropic.

We will apply “pleiotropy-robust” models as sensitivity analyses when sufficient independent genetic instruments are available (e.g. ≥ 10), given low statistical power of these models. These models include the weighted median
^
38
^, weighted mode
^
39
^ and MR Egger
^
40
^ regression and effect estimates from these methods can be compared to the IVW estimate obtained in initial analyses to evaluate if observed effects are possibly driven by horizontal pleiotropy. The weighted median can provide an unbiased causal estimate even when some of the genetic instruments used are invalid, the weighted mode effect estimate is more robust to horizontal pleiotropy, and the MR-Egger regression intercept can provide an indication of directional (i.e. unbalanced) pleiotropy. Whilst these sensitivity analyses relax certain assumptions of the IVW method, these models introduce new assumptions, so it is therefore important to use all three methods for comparison. If a consistent effect is observed across these three methods and the IVW estimate obtained from the main analyses, it is less likely that this finding is driven by violations of MR assumptions. To support these findings we will also use MR-PRESSO
^
41
^ to detect, and correct for, horizontal pleiotropy. This method assumes the majority of SNPs used as instruments are valid. 

For any exposures found to be associated with CRC risk, after applying an FDR correction, Steiger filtering will be used to explore the causal direction of SNP effects
^
42
^. The steiger_filtering function in the TwoSampleMR package will be used to evaluate if findings are driven by reverse causation, whereby the SNP used to instrument a molecular trait has an effect on CRC which in turn impacts variation in the molecular trait.

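### For cis instruments with a strong lead SNP, SNP-wise leave-one-out loses much of its ability to show that one variant drives the result

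*Protocol article*

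**What the plan says.** Under Exposure data and instrument selection, the protocol article states: "Genetic instruments will be constructed by selecting SNPs strongly associated with each trait of interest (p<5°10" to the power −8). Protein drug targets and biomarkers are limited to cis variants, and for these "we will increase the number of SNPs in our genetic instrument by permitting SNPs to be in weak linkage disequilibrium", with r² below 0.10 given as an example. The LD is handled at estimation by "using a generalised IVW method that can account for correlated instruments", with a correlation matrix from 10,000 UK Biobank participants. No conditional or joint test is stated for the added SNPs. SuSiE, which allows several causal variants, appears only under Colocalisation.

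Under Sensitivity analyses, every set with more than one SNP is re-analysed, "each time leaving out one SNP to test if there is a particular SNP that is driving results"; a horizontally pleiotropic SNP is named as one possible reason. No criterion for reading the result is given. The pleiotropy-robust models are applied "as sensitivity analyses when sufficient independent genetic instruments are available (e.g. ≥ 10").

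**The concern.** A SNP that is only a weak LD neighbour of a causal lead has the same ratio of CRC association to trait association as the lead. If such neighbours enter the set, dropping the lead does not remove its signal, because the neighbours still point to the same estimate. The check was included to show that one variant, perhaps a pleiotropic one, is behind the result. Here it can look reassuring when one variant is.

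This matters most for the drug rows. Cis sets will often fall short of about 10 independent SNPs, so the robust models would not be run. Colocalisation asks whether a causal variant is shared, and a pleiotropic shared variant would also support H4. A drug-target finding could then seem supported by several SNPs while resting on one variant.

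**Working it through.** **The plan's own total.** 78,473 + 107,143 = 185,616, as stated under Power.

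**When a neighbour qualifies through LD alone.** Two-sided p < 5×10⁻⁸ means |z| = 5.451, so F = 29.7. A non-causal SNP at LD r² with the lead has expected F of about r² × F(lead), so F(lead) must reach 29.7/r². With R² = F/(F + N − 2) and an assumed exposure N of 35,000:

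| LD r² | lead F needed | lead R² |
|---|---|---|
| 0.10 | 297 | 0.84% |
| 0.05 | 594 | 1.67% |
| 0.02 | 1,486 | 4.07% |

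At r² = 0.10, leads with the R² values in Figure 1 (0.05, 0.01, 0.005, 0.001) need exposure samples of about 5,600, 29,400, 59,100 and 297,000.

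**Effect on the main estimate.** With the lead in the set, generalised IVW gives pure LD neighbours an expected weight of zero. With SE(y) = 1/√(185,616 × 0.4228 × 0.5772) = 0.0047 per standardised genotype, the standard error is 0.0047/√R²: 0.047, 0.033 and 0.021 at lead R² of 1%, 2% and 5%, the same as for the lead alone.

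**Effect of dropping the lead.** With k neighbours at LD r², conditionally independent given the lead, the information kept is k·r²/(1 + (k − 1)·r²). At r² = 0.09:

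| k | information kept | SE ratio | lead z of 4 becomes | lead z of 6 becomes |
|---|---|---|---|---|
| 1 | 0.090 | 3.33 | 1.20 | 1.80 |
| 3 | 0.229 | 2.09 | 1.91 | 2.87 |
| 5 | 0.331 | 1.74 | 2.30 | 3.45 |
| 9 | 0.471 | 1.46 | 2.74 | 4.12 |

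The expected estimate is unchanged; only precision falls. In simulations with a lead F of 400 to 3,000, the median estimate without the lead was 0.92 to 1.02 of the lead's ratio.

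**One causal variant, simulated.** Assumptions: N 35,000, LD r² 0.02 to 0.10, 5 or 10 neighbours, CRC effect wholly pleiotropic. Among significant results from sets of at least two SNPs, every leave-one-out run kept its sign and p < 0.05 in about 16-83% at lead R² 1%, 29-100% at 2% and 62-100% at 5%, over apparent odds ratios 0.9 to 0.7. The low ends belong to odds ratio 0.9, where the lead's own z at R² 1% is only 0.105/0.047 = 2.2. If non-significant full results are counted as failures, odds ratio 0.9 at R² 1% gives about 7-12%.

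**Two signals, one pleiotropic and one with no CRC effect.** Under the random-effects IVW that Main analyses prescribes above about three SNPs, SNP-wise leave-one-out kept sign and significance in about 8-100%, depending on the strength of the two leads. Dropping each lead with its LD partners let the false result through in about 1-6%, and kept a true odds ratio of 0.8 or 0.7 at both signals in 98-100%. One example shows the mechanism (lead F 1,000, lead CRC z of 4, one distinct null signal): without the lead, the estimate is 0.02 of the lead's ratio with no LD neighbours, but 0.80 with five.

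**The case against.** The strongest reply is that no reported effect is wrong. The plan anticipates the LD and corrects for it. A reader might infer that the extra SNPs double-count evidence and narrow the interval; they do not, because generalised IVW gives them essentially no weight beside the lead. That part of the reply stands.

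A reader might also infer that leave-one-out will always pass. The protocol sets no pass rule, and on significance the check often does fail: with one or three neighbours and a lead CRC z of 4, significance survives in only 23% or 47% of significant runs. What hardly moves is the point estimate.

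Scope is narrow too. Five of the 21 traits in Table 2 are drug rows (LDL cholesterol via HMG-CoA reductase, IL23, ACE, and SBP via NCC and ADRB1); others count only if classed as biomarkers. Dietary and hormone sets use r² below 0.001, where a neighbour would need a lead F near 29,700. At N of 35,000, the two lower R² values in Figure 1 give lead F of about 35 and 176, below the 297 needed, so few such sets would gain neighbours.

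Other planned work helps in part. SuSiE and the regional plots can show whether a region holds one signal, and multivariable MR may be explored where instruments overlap. None of them excludes a pleiotropic shared variant, and none changes how leave-one-out is run.

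Finally, a reader might think the inflated SNP count also matters for the choice between fixed and random effects ("The multiplicative random effects IVW will be prioritised, except where the number of SNPs is limited (e.g. ≤3"). No numerical consequence of that has been shown, so it forms no part of this point.

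**Conclusion.** The point holds as a limited weakness in one sensitivity analysis, not as an error in the main estimate. For cis sets with a lead F of about 300 or more, the stated selection rule admits neighbours that carry only the lead's signal, and SNP-wise leave-one-out then loses much of its ability to expose a single driving variant. The near-constant point estimate follows from the algebra when there is one causal variant. The survival rates for significance are conditional on exposure sample size, number of neighbours, lead R² and effect size, none of which the document fixes for any trait; the wide ranges should be read in that light. The document does not support saying that every cis row is affected or that any result would be reported as robust. The change is a cheap improvement, worthwhile because it alters what can be concluded from the check.

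**What to change.** In Sensitivity analyses, run leave-one-out for cis sets by distinct signal, dropping each lead together with its LD partners. Define signals by conditional or joint analysis of the summary statistics, using the UK Biobank reference panel already planned. Report the number of distinct signals for each drug-target or biomarker row. Where there is only one, present the result as single-variant evidence and do not cite leave-one-out as support.

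The cost is one conditional analysis per cis region and a few lines of text. Virtually no precision is lost, since LD neighbours add essentially none. Some drug rows will lose apparent multi-SNP support. The change does not detect pleiotropy in a single-signal region, where the estimate stays the same; it only removes a false reassurance. It gains real detection only where there are two or more signals.
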